## Appendices

### Appendix 1

#### A Standard off-pump (OPCAB) procedure

1. Full median sternotomy is used in all patients

2. Graft material is harvested and controlled

3. Heparin is given and the Activated Clotting time (ACT) is controlled. If necessary, additional heparin is given to achieve an ACT above 400 sec. before arteriotomy.

4. Autotransfusion or cellsaver is used to avoid blood spill.

5. Opening of the pericardium

6. Devices for mobilization and stabilizing the heart are positioned

7. The vessel is opened

8. An intracoronary shunt is placed and/or CO- blower may be used. If necessary, a snare can be placed proximally but not distally to the anastomosis

9. The anastomosis is made with prolene 7.0 running suture

10. The proximal anastomoses are performed either before or after performing the distal anastomosis with minimal manipulation of the aorta. Bilateral internal mammary artery grafts, Y-grafts can be used but also proximal anastomosis devices and side-clamping are allowed.

11. Flow in coronary grafts is controlled using transit-time flow meter and registered. Eventual redo of the anastomosis is at the surgeon's discretion.

12. Two atrial and two ventricular pace electrodes are placed.

13. After the procedure, 4 mg of protamin is given and if necessary additional protamin in order to fully revert the heparinization to ACT level below 120 s.

14. Drainage tubes are placed.

i) Sternum is closed with wires and fascia, subcutis and skin closed with sutures.

#### B Standard CCABG procedure

1. Full median sternotomy is used in all patients

2. Graft material is harvested and controlled

3. Heparin is given and the Activated Clotting time (ACT) is controlled. If necessary, additional heparin is given to achieve an ACT above 400 sec. before arteriotomy.

4. The pericardium is opened and pericardial sutures are placed to expose the heart.

5. Cannulation of right atrium and aorta. Start of cardiopulmonary by-pass.

6. When the heart is fully relieve, the places where to place the anastomoses is marked.

7. Cross-clamping of the aorta

8. Cold antegrade or retrograde cardioplegic solution is given. Both crystalloid and hemocardioplegia are accepted

9. Graft material is prepared for anastomosis when asystoli has occurred and the ordered amount of cardioplegic solution is given, distal anastomoses are made using 7.0. prolene running suture.

10. Patency and tightness of the anastomosis are tested using cardioplegic solution if distal anastomoses are performed before proximal anastomoses.

11. The proximal anastomoses are performed either before or after performing the distal anastomosis. Bilateral internal mammary artery grafts, Y-grafts can be used but also proximal anastomosis devices and side-clamping are allowed.

12. Flow in coronary grafts is controlled using MediStim Transit-time flow meter and registered. Eventual redo of the anastomosis is at the surgeon's discretion.

13. Extra-corporeal circulation is gradually decreased and stopped. Test-dose of protamin is given.

14. Decannulation.

15. After the procedure, protamin is given to fully revert the heparinization to ACT level below 120 s.

16. Two atrial and two ventricular pace electrodes are placed.

17. Drainage tubes are placed.

18. Sternum is closed with wires and fascia, subcutis and skin closed with sutures.

### Appendix 2. Anaesthesia

The aim is that all patients receive a standard anesthesia and perioperative treatment, to minimize the influence of anesthesia and perioperative care in the included patients.

The following is recommendated guidelines. There will be slight differences between the involved hospitals, but it is mandatory for each hospital to secure, that there will be no differences is anesthesia and perioperative care between the two groups (OPCAB and CCABG).

#### Premedication

Peroral midazolam 3.75–7.5 mg one hour prior to surgery. If the patient receives treatment with beta-blocker, the usual dose is given at the same time.

#### Anesthesia

Intravenous induction with midazolam (0.05–0.15 mg/kg) and fentanyl (5–15 μg/kg); muscle relaxation with rocuronium (0.6 mg/kg). Anesthesia shall be maintained with either inhalation of sevoflurane or desflurane to improve ischemic preconditioning and with additional boluses of fentanyl (total dose, 20–30 μg/kg) and rocuronium. During cardiopulmonary bypass (CPB) the inhalation agent is given to the bypass circuit (Aarhus University Hospital, Aalborg and Odense University Hospital), alternatively an infusion of propofol is given to the bypass circuit (Aarhus University Hospital, Skejby and Gentofte Hospital). Aarhus University Hospital, Skejby will use total intravenous anesthesia due to lack of equipment for inhalation agent.

#### Monitoring

Arterial catheter; central venous catheter; pulmonary artery catheter for measuring of central venous pressure, pulmonary artery pressure and cardiac output, preferable a fiberoptic catheter shall be inserted for measuring of mixed venous saturation (S_V_O_2_), 5-lead ECG for measuring of heart rate and cardiac ischemia, peripheral oxygen saturation (S_p_O_2_), end-tidal carbon dioxide (CO_2_); Minimal alveolar concentration (MAC) of anesthetic inhalation agent; central body temperature (bladder); peripheral temperature; catheter in the bladder.

All parameters will be recorded continuously according to the flow chart in each department. Specific defined parameters will be recorded in the flow chart following the present study.

#### Temperature

Normothermia is defined as a central body temperature (bladder) of 35–37°C.

CABG group: The central body temperature shall be achieved by a heat-exchanger in the cardiopulmonary bypass circuit.

OPCAB group: The central body temperature shall be achieved by using warm intravenous fluids, a heating mattress, a warming blanket, in addition to maintaining a warm operation theatre.

#### Ventilation

Mandatory ventilation tidal volume 8–10 ml/kg and the rate adapted for a partial arterial pressure of CO_2 _(PaCO_2_) between 4.5 and 5.5 kPa, positive end-expiratory pressure (PEEP) at 5 cmH_2_O, and FiO_2 _at 0.4–0.6 to keep partial arterial pressure of oxygen (PaO_2_) above10 kPa. Patients with preoperative chronic obstructive lung disease shall at least be treated in accordance to their preoperative values of PCO_2 _and PO_2_.

Before closure of sternum, the lungs shall be inflated manually to reopen atelectasis due to pulmonary collapse during surgery.

Extubation as soon as the drainage loss in acceptable; the central body temperature is >36°C and peripheral temperature is >32°C; the circulation is stabilized with a mean arterial pressure > 70 mmHg, a cardiac index > 2.2 liters/minut/m^2 ^and a heart rate < 90/minute, and if measured a SvO_2_>60%; normocapnia and oxygenationindex (PaO_2_/FiO2) > 35.

After extubation in intensive care unit (ICU) the aim is a PO_2_>10 kPa achieved by supplementary treatment with either dry oxygen 1–5 litres/minute or humidified oxygen 15 litres/minute with FiO_2 _between 0.40 and 1.0.

#### Vasoactive drugs

Vasodilators: Nitroglycerine, nitroprusside, nifidipine.

Vasocontractors: Noradrenaline.

Inotropic agents: Epinephrine, dobutamine, dopamine, phosphodiesterase inhibitors, calcium sensitizer.

The vasoactive drugs are given on indication to secure optimal central and peripheral circulation. The drug of choice depends of the routine in the cardiac units.

#### Mechanical support

Intraaortic ballon pump and assist device is placed on indication depending on the routine in the cardiac units.

#### Volume substitution

Crystalloids: Isotonic saline, isotonic ringers acetate, isotonic potassium-glucose.

Colloids: Hydroxyethyl starch, dextran.

Blood products: On indication according to the recommendations on the centres.

Fluids are given to maintain normovolemia and hematocrite > 0.24.

#### Blood glucose

All patients, non-insulin dependent and insulin dependent diabetes as well as patients without diabetes shall have blood glucose monitored carefully during surgery and in ICU.

The goal of blood glucose level shall be:

Peroperative blood glucose: 6 – 10 mmol/l

Postoperative (ICU) blood glucose: 5 – 7 mmol/l

The maintenance of blood glucose level shall be achieved by infusion of glucose-insulin-potassium according to the regime in each hospital.

#### Postoperative sedation

Infusion of propofol 0.5–2 mg/kg/hour and incremental dosis of morphine 1–4 mg. Supplementary NSAID is given according to the regimes in the cardiac units.

#### Antiemetics

Bolus dose of metoclopramid or ondansetron on indication.

### Appendix 3. Postoperative treatment

Low molecular heparin: Fragmin 5000 IE × 1 untill 7th postoperative day or discharge from hospital

Acetyl-salicylic-acid: 75 mg × 1

#### Clopidogrel (Plavix)

75 mg × 1 for three months. Patients who have started clopidogrel treatment because of earlier implanted stent or because of acute myocardial infarction will continue the planned treatment. These patients shall also receive clopidogrel for at least 3 months postoperatively.

#### Statines

All patients shall receive treatment with statins. Thyroid and liver biochemical analyses are controlled before beginning treatment. In case of planned operations, treatment is paused at the day of admission to hospital but is started again before discharge

#### Acute operations

treatment is paused at the day of the operation but is started again before discharge.

#### Dose

Pravachol 40 mg × 1, Zocor 20–40 mg × 1, Simvastatin 40 mg × 1 or Zarator 10 mg × 1.

#### ACE-inhibitors

Shall be used in patients with left ventricular ejection fraction < 50%, congestive heart failure and/or arterial hypertension.

#### Betablockers

In patients with acute myocardial infarction within the last year and/or congestive heart failure.

#### Diuretics and potassium

Congestive heart failure with fluid retention and in some patients with arterial hypertension.

#### Amiodarone

In patients clinically affected by postoperative atrial fibrillation, initially a bolus of 300 mg is injected intravenously within 20 minutes, followed by infusion of 1200 mg the following 24 hours or untill conversion to sinus rhythm. Infusion through central venous catheter. Bolus injection can, however be performed through peripheral vein.

Subsequently, oral treatment is T. Cordarone 600 mg × 2 for one week, 400 mg × 2 second week, 200 mg × 2 third week and 200 mg × 1 during the fourth week followed by discontiuation of therapy in case of stable sinus rhythm.

### Appendix 4. Definitions

#### A. Postoperative acute myocardial infarction

1. Postoperative acute myocardial infarction: A peak creatine kinase-MB(CK-MB) of at least 75 ng/ml by day 3

2. New Q-wave evidence of MI, along with CK-MB of at least 50 ng/ml by day 3

3. New Q-wave evidence of MI by day 30 that was not present at day 3

4. MI (Q-wave or non-Q-wave) as defined by the World Health Organisation

#### B. Stroke

The World Health Organization's definition of stroke is used, i.e., an acute disturbance of focal or global cerebral function with symptoms lasting more than 24 hr or leading to death of presumed vascular origin.

Patients with the following ICD-10 discharge diagnosis codes in the Danish National Patient Registry are considered possible cases of stroke:

I 61 Intracerebral haemorrhage

I 63 Ischaemic stroke

I 64 Non-specified stroke

Patients with subdural haematoma, epidural bleeding, retina infarction or infarction caused by subarachnoidal bleeding, trauma, infection, surgery (not related to CABG or OPCAB surgery) or a intracerebral tumor are not classified as stroke patients. Moreover the definition does not include patients with only non-specific symptom, e.g. isolated dizziness or headache or asymptomatic patients with infarctions identified only by brain imaging.

Diagnostic work-up: In case of clinical symptoms of stroke or transient cerebral ischemia (TCI), symptoms should be noted in the patient file and the neurologist on duty should be asked to make a formal examination of the patient. All possible cases of stroke or TCI should undergo a brain imaging procedure, preferably a MR-diffusion scan. Should a MR-diffusion scan not be possible, efforts should be made for the patient to have a CT scan 3–7 days after the start of symptoms (even if a CT scan has been made in the acute phase).

#### C. Graft patency

The coronary angiogram is evaluated by two different cardiologists. The grafts are rated A: Open, B: Stenotic (more than 50%), O: Occluded, each for the 1) distal anastomosis, 2) proximal anastomosis og 3) length of the graft. Discrepancies are settled by conference.

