### Randomisation

The operating surgeon enters patients in a central database accessed by the internet. Before being able to randomise, the surgeon has to enter a preoperative plan including which coronary arteries are to be grafted, the conduit type and whether a single, sequential, or y-graft is planned. Having done this the patient is subsequently randomised either to OPCAB or CCABG by the on-line system

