### Secondary endpoints

a) A combined end-point of death + stoke + myocardial infarction during follow-up

b) Patency of by-pass grafts assessed by coronary angiography 6 months after the operation.

c) Total mortality and cardiac mortality during follow-up.

d) Need of new intervention for cardiac angina during follow-up.

e) Quality of life assessed by MOS SF-36 and EuroQol questionnaires 6 months and 3 years after the operation.

f) Total hospital costs and costs of public care provided 6 months and 3 years after the operation and difference in costs per quality adjusted life year.

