### Analysis

Kaplan-Meier plots will be used for graphic comparisons between groups and log- rank test for numerical comparison. Data analysis will be performed in accordance with the principle of intention-to-treat. An interim analysis will be performed for monitoring the accumulating data during the planned study period, i.e., after half of the patients have been recruited. The O'Brien-Fleming approach will be used in these analyses. At the interim analysis a p-value below 0.5% will be considered significant, while a p value below 4.8% will be considered significant after conclusion of the study. In this manner, a 5% level of significance is sustained. For the 6 months and 3 years data, Kaplan-Meier plots will be used for graphic comparisons between groups and log- rank test for numerical comparison.

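### Graft patency is rated graft by graft, but the protocol fixes no unit of analysis, and the only test named for 6-month data assumes independent units

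*Protocol article*

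**What the plan says.** - **Unit of randomisation** (Randomisation): the patient. After the surgeon has entered the operative plan, "the patient is subsequently randomised either to OPCAB or CCABG by the on-line system".
- **Several grafts per patient are foreseen** (Randomisation): the plan must state "which coronary arteries are to be grafted, the conduit type and whether a single, sequential, or y-graft is planned". The expected number of grafts per patient is not given.
- **Endpoint** (Secondary endpoints, item b): "Patency of by-pass grafts assessed by coronary angiography 6 months after the operation".
- **Rating** (Appendix 4, C. Graft patency): "The grafts are rated A: Open, B: Stenotic (more than 50%), O: Occluded, each for the 1) distal anastomosis", and then for "2) proximal anastomosis og 3) length of the graft". Each graft can therefore carry three ratings. No rule turns them into one status per graft or per patient.
- **Test** (Analysis): "For the 6 months and 3 years data, Kaplan-Meier plots will be used for graphic comparisons between groups and log- rank test for numerical comparison". Clustering of grafts within patients is not mentioned.

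**The concern.** The endpoint and its rating are both expressed in grafts, while allocation is by patient. Grafts in one patient share the surgeon, the operation and the postoperative antithrombotic regimen. Anastomoses on a sequential or Y-graft also share an inflow, so one failure can affect several of them. Positive correlation within a patient is therefore plausible. An ordinary log-rank test applied to grafts ignores it, and the standard error of the difference between arms comes out too small.

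Patency is a stated secondary aim. The Background reports that earlier trials disagree on it, one recent study having found significantly lower patency after off-pump surgery. An overstated significance claim, in either direction, would add to that dispute rather than settle it.

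**Working it through.** **The plan's own figures.** No power or precision figure is given for patency. The only one in the protocol, 82% power, concerns the 30-day primary endpoint. It reproduces closely: Φ((0.005 + 0.08 − 0.04)/√((0.08×0.92 + 0.04×0.96)/450) − 1.96) = Φ(2.852 − 1.960) = 81.4% at one-sided 2.5%. It has no bearing on this point.

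**Inputs**

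- From the protocol: 450 patients per arm; patients randomised; grafts rated individually.
- Assumed, because the protocol gives neither: m = 3 grafts per patient, and ICC = 0.05, 0.1, 0.2 or 0.3.

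**Formulas for a graft-level test that ignores clustering**

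- Design effect: DE = 1 + (m − 1) × ICC.
- The correct standard error is √DE times the naive one.
- True two-sided level of a nominal 5% test: 2 × (1 − Φ(1.96/√DE)).

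| ICC | DE | √DE | 1.96/√DE | True level |
|---|---|---|---|---|
| 0.05 | 1 + 2×0.05 = 1.1 | 1.049 | 1.869 | 6.2% |
| 0.1 | 1 + 2×0.1 = 1.2 | 1.095 | 1.789 | 7.4% |
| 0.2 | 1 + 2×0.2 = 1.4 | 1.183 | 1.656 | 9.8% |
| 0.3 | 1 + 2×0.3 = 1.6 | 1.265 | 1.550 | 12.1% |

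A correct confidence interval is wider by √DE − 1, which is 4.9%, 9.5%, 18.3% and 26.5% in turn. If the final threshold of 4.8% were applied to this endpoint, the true levels would be 5.9%, 7.1%, 9.5% and 11.8%.

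**Sensitivity to the number of grafts.** Over the same ICC range, 2 grafts per patient give 5.6% to 8.6%, and 4 grafts give 6.8% to 15.5%.

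**Check by simulation.** No true difference, 450 patients per arm, 2, 3 or 4 grafts with probabilities 0.25, 0.5 and 0.25, 15% of grafts occluded (assumed), beta-binomial correlation, 4,000 runs. The log-rank statistic was computed with all grafts read at one time.

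| ICC | Log-rank on grafts | Any occluded graft, per patient | Grafts, patient-clustered variance |
|---|---|---|---|
| 0 | 5.0% | 5.2% | 5.2% |
| 0.05 | 6.0% | 5.0% | 4.8% |
| 0.1 | 7.5% | 5.2% | 4.6% |
| 0.2 | 9.9% | 5.3% | 5.1% |
| 0.3 | 13.0% | 5.4% | 4.9% |

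At ICC 0.3 the simulated 13.0% lies a little above the formula's 12.1%, largely because graft numbers vary. The size-weighted mean is (0.25×4 + 0.5×9 + 0.25×16)/3 = 3.17 grafts, so DE = 1 + 2.17×0.3 = 1.65 and the level is 12.7%. Both remedies hold the level close to 5%.

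**The case against.** The strongest objection is that the protocol never says patency is tested per graft. Appendix 4 C tells two cardiologists how to read an angiogram; it does not say what is compared between arms. Ratings collected per graft can feed a per-patient outcome, which has no clustering problem. This stands, and it makes the inflation conditional. A reader might infer that the protocol prescribes a per-graft log-rank test and that its false-positive rate is therefore inflated. The text does not go that far.

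Second, the log-rank sentence may be meant only for clinical events. Quality of life and costs are also collected at 6 months and 3 years, and a log-rank test suits neither. This is a fair reading of the intention. Taken literally, however, the sentence covers patency. Items b, e and f are the only secondary endpoints tied to the 6-month point, whereas a, c and d refer to follow-up in general. No other method is named for patency.

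Third, the unit of analysis and robust standard errors are often left to an analysis plan, which is not shown here. Silence alone would not be a finding. But this protocol does name a method for 6-month data, and that method does not suit a graft-level endpoint.

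Fourth, the size rests on assumptions. That is correct: neither grafts per patient nor the ICC is in the protocol. Under a graft-level test the direction needs only a positive correlation. A reader might also infer that every site rating counts as a separate unit, which would give a much larger inflation. Nothing in Appendix 4 C suggests this, so no figure on that basis is offered.

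**Conclusion.** The point holds in a conditional form. The protocol defines and rates patency by graft, randomises patients, names only an independence-assuming test for 6-month data, and leaves the unit of analysis open. If grafts are the unit and the log-rank sentence is applied as written, a nominal 5% test has a true level of about 6% to 12%, assuming 3 grafts per patient and an ICC of 0.05 to 0.3. If patency is summarised per patient, there is no inflation from this source. Only one secondary endpoint is concerned; the 30-day primary endpoint and its power calculation are untouched. A clarification is warranted, but the documents do not show that an invalid patency test was definitely planned.

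**What to change.** In the Analysis section, exclude patency from the sentence on 6-month and 3-year data and give it its own statement. Choose one of:

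- a patient-level outcome, such as any occluded graft, compared between arms with one observation per patient; or
- a graft-level comparison using GEE or patient-clustered robust standard errors, reporting the risk difference with its confidence interval.

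In Appendix 4 C, add one prespecified rule for combining the three site ratings into a single graft status. The worst of the three is a simple candidate, but the protocol does not dictate any particular rule.

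Cost: wording only, with no new data. The graft-level interval becomes about 5% to 26% wider under the assumptions above, which is the precision the data actually support. An any-occluded-graft outcome depends on how many grafts each patient receives, so graft numbers should be reported by arm alongside it.
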